### Interventions

2.9

Treatment strategies will be developed by consensus with experienced acupuncture practitioners and a neurologist. The trial is to include three groups: the CEA group, the combined group, and the rTMS group. The basic supplement regimen is as follows: 1000-1200 mg of calcium per day is recommended, which can be achieved through dietary intake or supplements. It is important to note that dietary calcium intake is recommended, but if dietary intake is insufficient, supplements can be used to compensate. Vitamin D intake of 800–1,000 international units (IU) per day is also recommended (29).

#### Study schedule

2.9.1

Baseline information on age, menopause age, weight, education, vital signs, and duration of illness will be collected and recorded (Table 1). Then, the primary outcomes will be the changes in BMD scores and total efficiency of Chinese Medicine Symptoms before and after treatment. Secondary outcomes will include the SF-MPQ, OSS, MMSE, and BDI-II every 4 weeks for 12 weeks of treatment and 8 weeks follow-up period. Adverse events that occur during the trial will be recorded. The leptin, leptin receptor, and norepinephrine levels of peripheral blood must be measured before and after treatment.

**Table 1 tab1:** Trial flow and schedule: enrollment, interventions, and assessments.

Research stage			Duration of treatment (weeks)				Follow-up period (weeks)	
Inclusion/exclusion criteria			0	4	8	12	4	8
Sign the informed consent form			√					
		General information	√	√	√	√		
		Previous medical history	√					
		Clinical symptoms and physical signs	√	√	√	√		
Physical examination		Tongue manifestation, pulse, manifestation, weight	√			√		
		Vital signs: T, BP, P, R.	√			√		
Security check		Electrocardiogram	√			√		
		Liver function	√			√		
		Renal function	√			√		
		Blood lipids	√			√		
Intervention		CEA						
		rTMS						
		CEA combined with rTMS						
Efficacy indicators	Primary outcome	①BMD	√			√			②Total efficiency of Chinese Medicine Symptoms	√			√		
		③SF-MPQ	√	√	√	√	√	√
		④OSS	√	√	√	√	√	√
	Secondary outcome	⑤Leptin	√			√		
		⑥Norepinephrine	√			√		
		⑦Leptin receptor	√			√		
		⑧MMSE	√	√	√	√	√	√
		⑨BDI-II	√	√	√	√	√	√
Blood sample collection			√			√		
Randomization			√					
General assessment	Clinical efficacy					√		
	Compliance assessment		√	√	√	√		
	Adverse event		√	√	√	√		
	Safety evaluation		√			√		

T, Temperature; BP, Blood Pressure; P, Pulse; R, Respiration; CEA, Catgut Embedding in Acupoints; rTMS, repetitive Transcranial Magnetic Stimulation; BMD, Bone Mineral Density; SF-MPQ, McGill Pain Questionnaire Short-Form; OSS, Osteoporosis Symptom Score; MMSE, Mini-Mental State Examination; BDI-II, Beck Depression Inventory-II.

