**Method:**

This trial is a prospective and randomized controlled trial. 96 PMOP participants will be randomized in a 1:1:1 ratio into a CEA group, an rTMS group, or a combined one. Participants will receive CEA, rTMS, or combined therapy for 3 months with 8 weeks of follow-up. The primary outcomes will be the changes in Bone Mineral Density scores, total efficiency of Chinese Medicine Symptoms before and after treatment. Secondary outcomes include the McGill Pain Questionnaire Short-Form, Osteoporosis Symptom Score, Mini-Mental State Examination, and Beck Depression Inventory-II. The leptin, leptin receptor, and norepinephrine levels of peripheral blood must be measured before and after treatment. Adverse events that occur during the trial will be recorded.

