#### The CEA group

2.9.2

Our treatment method is based on previous literature reports (30).

The treatment group will undergo 12 weekly sessions of CEA for 3 months. The primary acupoints will be BL23, SP6, and RN4, with additional acupoints like BLI8, GB39, BL11, BL20, and ST36 added, depending on whether the case is a liver-kidney deficiency or kidney yang deficiency. During each treatment, RN4 is essential, while the other acupoints can be alternated between the left and right sides. The acupoint location method will follow the State Bureau of Technology Supervision standards. In addition, the operating procedure will be based on the National Standards of GB/T 21709.10–2008 manipulations of acupuncture and moxibustion, Part 10 Acupoint catgut embedding. Detailed information about the intervention group and acupoint location can be found in Tables 2, 3 of the STRICT checklist for reporting interventions in clinical acupuncture trials (Tables 2, 3).

**Table 2 tab2:** Acupoints selection.

Primary point	Additional point	
	Deficiency of liver and kidney	Deficiency of kidney yin
Shenshu (BL23) Sanyinjiao (SP6) Guanyuan (RN4)	Dazhu (BL11) Ganshu (BL18)	Xuanzhong (GB39) Zusanli (ST36) Pishu (BL20)

**Table 3 tab3:** Acupoints location.

Point	Location
BL23	1.5 cun lateral to the depression below the spinous process of the second lumbar vertebra
SP6	Posterior to the mesial border of the tibia and 3 cun above the tip of the medial malleolus
RN4	On the anterior midline, 3 cun below the umbilicus
BL18	1.5 cun lateral to the depression below the spinous process of the 9th thoracic vertebra
BL11	1.5 cun lateral to the lower border of the spinous process of the first thoracic vertebra
GB39	3 cun above the tip of the external malleolus, on the anterior border of the fibula
ST36	3 cun directly below Dubi (the lateral depression of the knee-joint) and one middle finger-breadth lateral to the anterior border of the tibia
BL20	1.5 cun lateral to the depression below the spinous process of the 11th thoracic vertebra

Cun=an acupuncture measurement unit; 1 cun corresponds to the study subject’s thumb width.

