#### The rTMS group

2.9.3

The treatment will be completed by a trained professional therapist using a transcranial magnetic stimulator (YRD CCY-II from Wuhan Eredo). The motor threshold (MT) and dorsolateral frontal lobe (DLPFC) stimulation site are to be determined during the first treatment. The room temperature will be maintained at 16°C–23°C, and the patient will be lying flat on their side on the treatment bed. The motor-evoked potentials (MEPs) are to be recorded in the contralateral hand’s interosseous muscle through the magnetic stimulator’s electromyographic amplifier, with the center of the “8” coil placed on the right temporal cortex of the subject. The stimulation site and the stimulation volume are adjusted until at least 5 out of 10 stimulations evoke MEPs with an amplitude more significant than 50 μV, at which point the magnetic flux is MT, and move 4 cm forward horizontally at the site where the MEPs are elicited, which is the DLPFC. We plan to utilize a positioning cap and a transcranial magnetic stimulator (YRD CCY-II from Wuhan Iredell) to accurately identify and target the specific location during the procedure (31). We intend to choose the right DLPFC point as the stimulation site. The stimulation intensity will be set at 80% of the resting movement threshold, with a frequency of 1 Hz, lasting 30s with an interval of 4 s, and 10 series to be performed continuously on the patient (32, 33). The treatment plan will consist of one session per day, 5 days a week, for 4 weeks (34, 35). Starting from the fifth week, the treatment plan changes to twice a week for eight consecutive weeks (36). In total, this treatment plan will last for 12 weeks and include 36 sessions.

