##### Mild reactions

2.9.5.1

Local aseptic inflammatory reactions, such as redness, swelling, heat, and pain, often occur within 1–5 days.Systemic reactions may include a rise in body temperature within 4–24 h after treatment and an increase in blood count, which usually returns to normal in 3–5 days.

Most of the mild reactions are physiological after the treatment, do not need to be treated, and can be relieved on their own within a short period.

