#### Clinical manifestation

2.11.1

SF-MPQ and OSS will be measured every four weeks for 5 months. All evaluation indicators will be assessed at six time points: baseline, mid-treatment (4 and 8 weeks of treatment), post-treatment (12 weeks), and 1 month and 2 months after the treatments.

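### Table 1 schedules adverse-event recording only to week 12, so the last 8 of the trial's 20 weeks have no scheduled safety collection

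*Protocol article*

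**What the plan says.** The commitment to record is general. Both the abstract (Method) and section 2.9.1 (Study schedule) say "Adverse events that occur during the trial will be recorded", with no end date.

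The abstract gives the length of the study: "Participants will receive CEA, rTMS, or combined therapy for 3 months with 8 weeks of follow-up". Section 2.11.1 (Clinical manifestation) places assessments at baseline, during treatment, and "post-treatment (12 weeks), and 1 month and 2 months after the treatments".

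Table 1 is more specific. Its "Adverse event" row is ticked at treatment weeks 0, 4, 8 and 12 and is empty in the two follow-up columns (4 and 8 weeks). The safety-evaluation row is ticked only at weeks 0 and 12. The SF-MPQ, OSS, MMSE and BDI-II rows are ticked in all six columns.

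Both treatments run for about 12 weeks. For embedding, "The treatment group will undergo 12 weekly sessions of CEA for 3 months" (2.9.2). For rTMS, "this treatment plan will last for 12 weeks and include 36 sessions" (2.9.3). On expected reactions, section 2.9.5.1 says "Local aseptic inflammatory reactions, such as redness, swelling, heat, and pain, often occur within" 1 to 5 days. Section 2.9.5.2 adds secondary infection, nerve injury, bleeding and thread allergy.

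**The concern.** The text promises recording across the trial, while the schedule that staff would work from stops at the end of treatment. Participants are still being assessed 4 and 8 weeks later, so the gap does not come from a lack of contact.

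Safety is a stated aim in the Introduction, and the combination is hypothesised there to reduce reactions. Adverse-event counts therefore bear on one of the trial's own hypotheses. Embedding leaves absorbable suture in tissue to give a prolonged stimulus, so exposure does not end on the day of the last session. Section 2.13 also states that there will be no dedicated data safety and monitoring committee, which gives routine scheduled recording more weight.

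If events after week 12 are picked up only when a participant volunteers them, late or lingering reactions may be under-counted. Thread is used in two of the three arms, so thread-related under-counting need not fall equally on all arms.

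**Working it through.** **Inputs.** Treatment of 12 weeks and follow-up of 8 weeks (abstract; Table 1). Six assessment columns in Table 1. Adverse-event ticks at weeks 0, 4, 8 and 12. Twelve weekly embedding sessions (2.9.2). Local reactions at 1 to 5 days (2.9.5.1).

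**Step 1: does treatment really run to week 12?** Section 2.9.3 gives rTMS 5 times a week for 4 weeks, then twice a week for 8 weeks: 4 × 5 + 8 × 2 = 36 sessions over 4 + 8 = 12 weeks. This reproduces the stated 36 sessions and 12 weeks.

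**Step 2: coverage of the observation period.**
- Total observation: 12 + 8 = 20 weeks.
- Weeks after the last scheduled adverse-event record: 20 − 12 = 8.
- Share without scheduled collection: 8 / 20 = 40%.
- Scheduled time points: 4 of 6.
- With ticks at both follow-up points: 6 of 6 time points and 20 of 20 weeks.

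**Step 3: is the blank row a reading fault?** It does not look like one. The adverse-event row keeps two empty trailing cells in the positions where the SF-MPQ, OSS, MMSE and BDI-II rows carry ticks.

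**Step 4: is the reaction window after the final embedding covered by the week-12 record?** The article does not date the sessions, so this needs an assumption. Count baseline as day 0 and week 12 as day 84.

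| Assumption | Last embedding | Days 1–5 after it | Covered by the week-12 record? |
|---|---|---|---|
| First session at week 0 | 11 × 7 = day 77 | days 78–82 | Yes, the window closes before day 84 |
| First session at end of week 1 | 12 × 7 = day 84 | days 85–89 | No |
| Week-12 record made the day after the last embedding | record on day 1 of the window | days 2–5 still to come | Only day 1 of 5 |

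The third row is possible because section 2.11.2 takes the closing blood samples on the day following the end of treatment. The article does not say that adverse events are recorded at that blood draw.

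**Step 5: does any other section set a collection window?** None does. Section 2.13 appoints safety inspectors to follow up and report adverse events but gives no period.

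**The case against.** **The word trial is ambiguous.** Section 2.5 speaks of completing the trial within 12 weeks ± 5 days. On that reading, recording during the trial and ticks up to week 12 agree. This has some force, but the usage is not consistent: section 2.5.4 lists loss in the follow-up period as a ground for discontinuation, and the abstract attaches the 8 weeks to the study. On either reading those 8 weeks have no scheduled collection.

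**A blank cell is not a ban on recording.** The general sentence in 2.9.1, the safety inspectors and the data safety and monitoring plan mentioned in 2.13 could all capture later events, and that plan is not shown. This stands. A reader might infer that events after week 12 will be missed; the documents support only that their collection is not scheduled.

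**The final embedding may be covered.** A reader might infer that the reaction window after the last session is unobserved for everyone who receives thread (2 × 32 = 64 of 96). That does not follow: if sessions start at week 0, the week-12 record falls after the window closes.

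**The bias is not shown.** The collection gap is the same in all three arms. The combined arm receives the same embedding regimen as the embedding-only arm (2.9.4), so loss of late thread reactions should be similar in those two. Only comparisons with rTMS alone are plausibly affected, and the documents give no figure for the size.

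**The timings given are short.** Where sections 2.9.5.1 and 2.9.5.2 give times, they run from hours to a few days, and none points to reactions 4 to 8 weeks after treatment. This also stands: 40% of the weeks is not 40% of the events. Thread allergy and nerve injury, however, are listed without any timing.

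**Conclusion.** The point holds as a gap in scheduled safety collection and a mismatch between the text and Table 1. Its measurable size is 8 of 20 weeks (40%), or 2 of 6 assessment points, without a scheduled adverse-event record. That figure rests only on the printed schedule.

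The effect on the results is not quantified. Delayed or persistent reactions would depend on spontaneous reporting, as would local reactions after a final embedding held close to the week-12 visit. Any under-count could affect comparisons with the rTMS-only arm; the documents give no ground for expecting it to distort combination against embedding alone. The documents therefore do not support a statement that the safety comparison is biased.

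The correction is still worth making, because safety is a stated aim, thread remains in tissue after the last session, and the assessments at which the question could be asked already exist.

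**What to change.** 1. In Table 1, tick the adverse-event row at follow-up weeks 4 and 8, and add the matching item to the case report form. The question at follow-up week 4 should cover the whole interval since the week-12 record, so that reactions after the final embedding are captured wherever that session falls.
2. In section 2.9.1, state the collection window explicitly: first treatment to follow-up week 8.
3. In section 2.14, state that the safety analysis counts events over that same window in all three arms.

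The cost is one question at two assessments that already take place, plus a short amendment. No visit, sample-size figure or treatment changes. Section 2.16 says that recruitment is under way, so an early change limits the number of participants whose follow-up is recorded under the old schedule. Any such participants should be identified when the safety data are reported.

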#### The CEA group

2.9.2

Our treatment method is based on previous literature reports (30).

The treatment group will undergo 12 weekly sessions of CEA for 3 months. The primary acupoints will be BL23, SP6, and RN4, with additional acupoints like BLI8, GB39, BL11, BL20, and ST36 added, depending on whether the case is a liver-kidney deficiency or kidney yang deficiency. During each treatment, RN4 is essential, while the other acupoints can be alternated between the left and right sides. The acupoint location method will follow the State Bureau of Technology Supervision standards. In addition, the operating procedure will be based on the National Standards of GB/T 21709.10–2008 manipulations of acupuncture and moxibustion, Part 10 Acupoint catgut embedding. Detailed information about the intervention group and acupoint location can be found in Tables 2, 3 of the STRICT checklist for reporting interventions in clinical acupuncture trials (Tables 2, 3).

**Table 2 tab2:** Acupoints selection.

Primary point	Additional point	
	Deficiency of liver and kidney	Deficiency of kidney yin
Shenshu (BL23) Sanyinjiao (SP6) Guanyuan (RN4)	Dazhu (BL11) Ganshu (BL18)	Xuanzhong (GB39) Zusanli (ST36) Pishu (BL20)

**Table 3 tab3:** Acupoints location.

Point	Location
BL23	1.5 cun lateral to the depression below the spinous process of the second lumbar vertebra
SP6	Posterior to the mesial border of the tibia and 3 cun above the tip of the medial malleolus
RN4	On the anterior midline, 3 cun below the umbilicus
BL18	1.5 cun lateral to the depression below the spinous process of the 9th thoracic vertebra
BL11	1.5 cun lateral to the lower border of the spinous process of the first thoracic vertebra
GB39	3 cun above the tip of the external malleolus, on the anterior border of the fibula
ST36	3 cun directly below Dubi (the lateral depression of the knee-joint) and one middle finger-breadth lateral to the anterior border of the tibia
BL20	1.5 cun lateral to the depression below the spinous process of the 11th thoracic vertebra

Cun=an acupuncture measurement unit; 1 cun corresponds to the study subject’s thumb width.

##### CEA group materials

2.9.2.1

Disposable sterile burying kit: provided by the Shenzhen Bao’an Hospital supply room of Traditional Chinese Medicine.Injection syringe: disposable sterile injection needle seven #(0.7*30 TWLB), Wuhan Wangguan Medical Equipment Co., Ltd.: State Food and Drug Administration Machinery (Quasi) No. 3151148, 2014.Absorbable surgical suture, multi-strand braided structured polyglycolic acid PGA suture, specification: 3–0 (20metric) 1.5 cm/20 segments, [Zhejiang Kandlai Medical Devices Co. No. 3151299].Andover 0.5% PVP-I Disinfectant Solution, Shenzhen Andover Disinfection High-Tech Co: Guangdong Health Disinfection Certificate (2016) No. 9087.Medical Sterilization Swabs, Shun Kangzheng, Model KZ3-12, Foshan Shunde Kangzheng Sanitary Material Co. Company: Guangdong Food and Drug Administration Machinery Production License 20,010,167.Aseptic Dressing, Product No.: DF-needle eye, Zhejiang Chun’an County Renhe Medical Supplies Industry and Trade Co. Zhejiang Food and Drug Administration Machinery (Permitted) Word 2014 No. 2640695.

#### The rTMS group

2.9.3

The treatment will be completed by a trained professional therapist using a transcranial magnetic stimulator (YRD CCY-II from Wuhan Eredo). The motor threshold (MT) and dorsolateral frontal lobe (DLPFC) stimulation site are to be determined during the first treatment. The room temperature will be maintained at 16°C–23°C, and the patient will be lying flat on their side on the treatment bed. The motor-evoked potentials (MEPs) are to be recorded in the contralateral hand’s interosseous muscle through the magnetic stimulator’s electromyographic amplifier, with the center of the “8” coil placed on the right temporal cortex of the subject. The stimulation site and the stimulation volume are adjusted until at least 5 out of 10 stimulations evoke MEPs with an amplitude more significant than 50 μV, at which point the magnetic flux is MT, and move 4 cm forward horizontally at the site where the MEPs are elicited, which is the DLPFC. We plan to utilize a positioning cap and a transcranial magnetic stimulator (YRD CCY-II from Wuhan Iredell) to accurately identify and target the specific location during the procedure (31). We intend to choose the right DLPFC point as the stimulation site. The stimulation intensity will be set at 80% of the resting movement threshold, with a frequency of 1 Hz, lasting 30s with an interval of 4 s, and 10 series to be performed continuously on the patient (32, 33). The treatment plan will consist of one session per day, 5 days a week, for 4 weeks (34, 35). Starting from the fifth week, the treatment plan changes to twice a week for eight consecutive weeks (36). In total, this treatment plan will last for 12 weeks and include 36 sessions.

#### The CEA combined with rTMS group

2.9.4

Subjects in this group will receive both the CEA and the rTMS treatment according to the respective regimens of the two therapies.

#### Adverse events

2.9.5

##### Mild reactions

2.9.5.1

Local aseptic inflammatory reactions, such as redness, swelling, heat, and pain, often occur within 1–5 days.Systemic reactions may include a rise in body temperature within 4–24 h after treatment and an increase in blood count, which usually returns to normal in 3–5 days.

Most of the mild reactions are physiological after the treatment, do not need to be treated, and can be relieved on their own within a short period.

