#### Discontinuation criteria

2.5.4

a Subjects who have experienced a severe adverse reaction or event that prevents them from continuing to be under treatment;

b Subjects who develop severe comorbidity or other systemic serious medical conditions during the trial and are unable to persist;

c Subjects who have poor compliance and do not cooperate with the relevant treatment despite repeated explanations;

d Subjects who request to withdraw from the study on their own;

e Subjects who take other drugs privately during the treatment period, which may interfere with the study results;

f The patient lost during the follow-up period for various reasons.

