##### Severe reactions

2.9.5.2

Hot compresses can alleviate pain in the needling points.Local redness, swelling, pain, fever, and other inflammatory manifestations caused by secondary infection can be resolved within 3–4 days.Nerve injury can occur due to incorrect operation, over-stimulation, or carelessness but can be prevented carefully.Bleeding may happen because of puncturing blood vessels or excessive stimulation. Compression bandages can be used to stop bleeding.Local itching, redness, swelling, fever, etc., may be symptoms of an allergy to threads. Anti-allergic treatment can be given in such cases.

Appropriate actions are taken to address more severe reactions in accordance with the grading and management of adverse reactions in CEA (37). Effective measures include discontinuation of the trial or ethically appropriate additional mechanisms.

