### Safety assessment

2.13

Current studies about rTMS have shown few side effects. Given that this study is a low-risk intervention, small sample clinical mechanism research trial, there is no need for a dedicated data safety and monitoring committee. To ensure the rights of participants and the smooth running of the trial, we have developed a data safety and monitoring plan based on the specificity of the disease, subject population, interventions, and outcome indicators of the study. After review by the Ethics Committee, safety inspectors are appointed to track, record, report, and deal with adverse events.

Therapists need to follow the CEA process strictly to ensure the concept of sterility and safety. Comply with the graded treatment of adverse reactions to CEA, assess and effectively identify the grade of adverse reactions in patients promptly, reduce the occurrence of adverse reactions and attenuate their harm, and deal with them promptly (37). Strictly exclude contraindications to rTMS treatment, sign an informed consent form, and complete a safety screening assessment. We intend to select the intensity, frequency, and number of rTMS stimulations according to the treatment purpose since the individual differences in resting motor threshold (RMT) determination. It should be strictly limited to safe sequences and avoid sequences that induce seizures and other risks. The assessment and effective management of adverse effects during treatment should be strictly controlled. Although the current rTMS treatment has a low risk, it is still necessary to prevent rTMS-induced seizures. It has been reported that rTMS can induce seizures in both standard and epileptic patients when the stimulation frequency is between 10 and 25 Hz and the stimulation intensity is above the threshold (38). For example, if a patient experiences a seizure, treatment should be stopped immediately, and first aid should be administered. Application of rTMS near the affected ear should be avoided in patients with hearing symptoms (e.g., tinnitus or phantom hearing).

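### Sections 2.9.5.1 and 2.9.5.2 class the same presentations as both mild and severe, mix cause with severity, and cover CEA reactions only, although safety is compared across three arms

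*Protocol article*

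**What the plan says.** Section 2.9.5.1 (Mild reactions) has two entries. The local one reads "Local aseptic inflammatory reactions, such as redness, swelling, heat, and pain, often occur within 1–5 days". The systemic one is "a rise in body temperature within 4–24 h after treatment and an increase in blood count, which usually returns to normal in 3–5 days". On handling it adds "Most of the mild reactions are physiological after the treatment, do not need to be treated".

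Section 2.9.5.2 (Severe reactions) has five entries: pain at the needling points ("Hot compresses can alleviate pain in the needling points"), secondary infection ("Local redness, swelling, pain, fever, and other inflammatory manifestations caused by secondary infection can be resolved within 3–4 days"), nerve injury, bleeding, and allergy to the threads with itching, redness, swelling and fever. It closes by referring action on more severe reactions to a cited grading of CEA reactions, with discontinuation among the possible measures.

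Section 2.13 (Safety assessment) repeats the instruction: "Comply with the graded treatment of adverse reactions to CEA". For rTMS it gives contraindication screening, a limit to safe stimulation sequences, a rule for seizure and a precaution for patients with hearing symptoms. It names no severity grade.

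Section 2.5.4(a) uses the word severe in a discontinuation criterion: "Subjects who have experienced a severe adverse reaction or event that prevents them from continuing to be under treatment".

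The Introduction states effectiveness and safety as aims and hypothesises that the combination reduces reactions. Table 1 schedules adverse-event recording at weeks 0, 4, 8 and 12 without restriction by arm.

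**The concern.** A severity class is useful only if two people who see the same event assign it to the same class. Here a sore implantation site fits an entry on each list, and so does a raised temperature. The headings promise severity, but the entries under them are largely sorted by what caused the reaction or what kind of event it is.

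This matters because safety is an aim and the hypothesis is comparative. A statement that the combined arm had fewer or milder reactions needs severity to mean the same thing in the CEA, rTMS and combined arms. The mild and severe lists describe needle and thread reactions, which can arise in only two of the three arms. The word severe also recurs in Section 2.5.4(a), so an inconsistent class carries over into a section on clinical conduct.

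**Working it through.** No arithmetic applies. The check sets the two lists side by side.

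| Presentation | Mild (2.9.5.1) | Severe (2.9.5.2) |
|---|---|---|
| Pain | Local, described as aseptic | At needling points, no cause given; also with infection |
| Redness, swelling | Local, described as aseptic | With infection; with thread allergy |
| Raised temperature or fever | Systemic, no cause given | With infection; with thread allergy |
| Local heat; raised blood count | Listed | Not listed |
| Itching | Not listed | With thread allergy |
| Nerve injury; bleeding | Not listed | Listed |

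1. **Signs.** Four signs appear on both lists: redness, swelling, pain, and raised temperature or fever. Neither list gives an intensity, extent or temperature threshold.

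2. **Cause.** Stated cause separates redness and swelling: aseptic on one side, infection or allergy on the other. It does not separate needling-point pain, whose severe entry states no cause. It separates temperature only in part, because the mild systemic entry names no cause.

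3. **Timing.** The 1–5 days for mild local reactions describe when they occur. The 3–4 days for infection describe when signs resolve. These are different quantities and should not be compared. The one comparable figure is the return to normal of mild systemic reactions in 3–5 days, and the 3–4 days lie inside it. Recovery time therefore does not separate the two classes of fever, and neither section offers it as a criterion.

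4. **Severity against cause.** Of the five severe entries, four (infection, nerve injury, bleeding, allergy) are defined by cause or kind of event. The fifth, needling-point pain, cannot be told from a mild entry. None is defined by how bad the reaction is. Bleeding is listed without regard to its amount, so a minor bleed falls under severe.

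5. **Coverage.** Section 2.9.5 follows the description of all three interventions and is headed as adverse events in general, but every entry is described as a needle or thread reaction. The grading cited in Sections 2.9.5.2 and 2.13 is for CEA.

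**The case against.** The strongest reply is that the lists do distinguish most entries. The mild local reactions are called aseptic, while the severe ones are attributed to infection or thread allergy, and nerve injury and bleeding appear only under severe. That stands. A reader might infer that an infected site is classed as mild as the text is written; it is not, because the word aseptic excludes it. The reply fails for needling-point pain, succeeds only in part for temperature, and leaves severity itself undefined.

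A second reply concerns stopping. A reader might infer that the severe label alone is grounds for discontinuation. The documents do not say so: Section 2.5.4(a) also requires that the reaction prevent further treatment, and Section 2.9.5.2 names discontinuation as one measure among others. Likewise, only most mild reactions are said to need no treatment.

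A third reply is that a journal article may leave adverse-event scales to the full protocol, and that the cited CEA grading and the data safety and monitoring plan mentioned in Section 2.13 are not shown. This is fair. The absence of an rTMS grade is not a finding by itself. A reader might also infer that the rTMS-only arm could register almost nothing. That is unsupported: no score is defined, adverse events are recorded in all arms, and Section 2.13 has an explicit rule for seizure. Hearing symptoms appear there as a precaution for patients who have them, not as a named harm of rTMS.

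What remains is an inconsistency in what the article does state.

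**Conclusion.** The point holds in a limited form. The stated classification contradicts itself on needling-point pain, places raised temperature or fever in both classes, and otherwise sorts mainly by cause under severity headings. Severity counts taken from it would not be reliable, and because it is specific to CEA it cannot by itself support a comparison of reaction severity across the three arms.

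The size is moderate: it should be corrected because safety is a stated aim and the correction is cheap. It does not affect BMD or the symptom outcome. The number of events that would be misclassified cannot be derived. Counts of treatment sessions would show exposure, not error, so none is offered as a measure of size.

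The conclusion assumes that the lists are used as printed to classify events. If the cited CEA grading or the unshown safety plan already replaces them with a severity scale for all arms, the remaining defect is the wording of the article.

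**What to change.** Reconcile Sections 2.9.5.1, 2.9.5.2, 2.5.4(a) and 2.13 so that one presentation leads to one class and the word severe means the same thing in each. Which class a given reaction belongs to, and how it is managed, is for the clinical team; no treatment or stopping rule is proposed here.

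For recording and between-arm reporting only, grade the severity of every adverse event in all three arms on one common scale, and enter suspected cause (for example aseptic reaction, infection, thread allergy, bleeding, nerve injury, rTMS-related) in a separate field. Base any statement about fewer or milder reactions with the combination on that common grade.

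The cost is protocol wording and one revised adverse-event page in the case report form. The reported event rate may rise, because minor complaints in every arm would be graded and counted. Section 2.16 says recruitment is under way, so events already recorded would need the two fields completed.
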